## Abstract

**Introduction:**

Shift workers are at a greater risk for obesity-related conditions. The impacts of working at night presents a challenge for designing effective dietary weight-loss interventions for this population group. The Shifting Weight using Intermittent Fasting in night-shift workers (SWIFt) study is a world-first, randomized controlled trial that compares three weight-loss interventions. While the trial will evaluate the effectiveness of weight-loss outcomes, this mixed-methods evaluation aims to explore for who weight-loss outcomes are achieved and what factors (intervention features, individual, social, organisational and wider environmental) contribute to this.

**Methods:**

A convergent, mixed-methods evaluation design was chosen where quantitative and qualitative data collection occurs concurrently, analyzed separately, and converged in a final synthesis. Quantitative measures include participant engagement assessed via: dietary consult attendance, fulfillment of dietary goals, dietary energy intake, adherence to self-monitoring, and rates for participant drop-out; analyzed for frequency and proportions. Regression models will determine associations between engagement measures, participant characteristics (sex, age, ethnicity, occupation, shift type, night-shifts per week, years in night shift), intervention group, and weight change. Qualitative measures include semi-structured interviews with participants at baseline, 24-weeks, and 18-months, and fortnightly audio-diaries during the 24-week intervention. Interviews/diaries will be transcribed verbatim and analyzed using five-step thematic framework analysis in NVivo. Results from the quantitative and qualitative data will be integrated via table and narrative form to interrogate the validity of conclusions.

**Discussion:**

The SWIFt study is a world-first trial that compares the *effectiveness* of three weight-loss interventions for night shift workers. This mixed-methods evaluation aims to further explore the effectiveness of the interventions. The evaluation will determine for who the SWIFt interventions work best for, what intervention features are important, and what external factors need to be addressed to strengthen an approach. The findings will be useful for tailoring future scalability of dietary weight-loss interventions for night-shift workers.

**Clinical trial registration:** This evaluation is based on the SWIFt trial registered with the Australian New Zealand Clinical Trials Registry [ACTRN 12619001035112].

## Introduction

1.

Shift workers make up an almost 30% subset of the workforce worldwide, who undertake critical work for a 24-h society to function (1). This essential work comes with a disproportionately greater risk for obesity, type 2 diabetes, and cardiovascular disease (2, 3). Night-shift workers fall within the highest risk category, with greater odds for these poor health outcomes (2, 3). Given the link between increased weight and metabolic conditions (4–6), weight loss is a logical target for reducing disease risk in this population. There is currently limited guidance for night-shift workers on best-practice dietary approaches for weight loss (7). Recent reviews on nutrition or weight-loss interventions for night-shift workers have identified a limited number of published studies and no statistically or clinically significant effect for weight loss (8). More research is needed to understand what dietary weight-loss interventions are best suited to night-shift workers (2, 9).

Night work is associated with metabolic misalignment, circadian disruption, and differences in 24-h energy expenditure compared to day workers, which in turn, is thought to contribute to weight gain (10). These factors offer a target for dietary weight loss approaches for night-shift workers. In order for weight loss interventions to be successful in the night-shift working population, meal timing may need to be considered in addition to energy restriction (10, 11). The Shifting Weight using Intermittent Fasting in night shift workers (SWIFt) study is a randomized-controlled (RCT), three-arm parallel intervention to compare the effectiveness of three dietary interventions on weight loss in night-shift workers, to investigate whether the timing of energy restriction is beneficial for night-shift workers (11). The SWIFt trial aims to investigate whether a 5:2 intermittent fasting approach that aligns two fast periods with night shift has benefits on both weight and metabolic outcomes (11). The 5:2 approach limits energy consumption to 20%–25% of energy requirements on two ‘fast’ days per week and *ad libitum* eating on the remaining 5 days (11). While the SWIFt RCT will examine the effectiveness of the dietary interventions for weight loss, it is now recommended evaluations are conducted alongside the trial to more fully understand the factors (both mechanisms of action and external influences) contributing to intervention effectiveness (12–18). This information is needed to improve effectiveness and to tailor future scalability of an intervention (12–18). Evaluations typically explore participant engagement to determine the extent to which the “active ingredients” or proposed mechanisms of action of an intervention can explain the study outcomes (13, 15). In addition, a key consideration in interventions involving human participants is *how* participants engage with the study requirements, that is, what drives participant “responsiveness” to the requirements of the intervention and leads to engagement (18). This allows a deeper understanding of what may drive participant engagement to a dietary intervention in a real-world setting.

Evaluations also typically explore whether contextual factors influence outcomes and underlying mechanisms (15). Contextual factors may be positive (enablers) or negative (barriers) and relate to different spheres of influence ranging from the individual (e.g., participant characteristics such as age or personality type), social (e.g., peer influence), and organisational (e.g., workplace environment), to the wider environment (19). An understanding of these underlying mechanisms and contextual factors in the SWIFt study will be useful to understand who can benefit the most from the interventions and to replicate the potential benefits in other non-research settings.

### Aims and research questions

1.1.

The overall aim of this study is to explore the contributing factors (intervention features, individual, social, organizational and wider environmental) to weight loss. Specifically:

To describe participant engagement overall and for each of the SWIFt weight loss interventions.Explore factors (intervention features, individual, social, organisational and wider environmental) that influence participant engagement for each of the SWIFt weight loss interventions.Explore for who weight change outcomes are achieved for each of the SWIFt weight loss interventions, and the influence of participant engagement.

## Intervention of interest

2.

The full study protocol has been described previously (11). In summary, shift workers will be randomized to one of three dietary interventions including: 20% continuous daily energy restriction (CER), versus 5:2D (day fast twice per week), versus 5:2N (night fast twice per week aligning with a night shift) for 24-weeks with a 12-month follow-up period. In the 5:2 interventions, participants will aim to limit intake for each fasting period to 2,100 kJ/day (females) or 2,500 kJ/day (males), providing a weekly energy restriction comparable to the CER intervention (i.e., 20%). Study participants will see a study dietitian fortnightly for the first 8 weeks and then monthly for the last 16 weeks of the intervention period and will be provided with study foods for 2 days per week. The dietitian will explain the dietary intervention, set goals with participants, discuss strategies to assist with dietary adherence, and monitor progress. At the conclusion of the 24-week intervention, participants will be given practical suggestions and food options for continuing their allocated dietary intervention. Participants will be followed up at 2-, 6- and 12-months’ time during the follow-up period to monitor progress. No food will be supplied to participants during this time.

## Methods and analysis

3.

This study uses “pragmatism” as a theoretical perspective guiding research design. Pragmatism is oriented to what works and choosing multiple, best-fit methods to answer the research questions posed (20, 21). A convergent, mixed-methods, experimental (or intervention) design (20) has been selected given that the purpose of this study is to evaluate a randomized controlled trial (experimental intervention). In addition, this design has been selected due to the timeframe of the SWIFt study, where the outcomes of the first set of quantitative data analysis will not be known until all participants have completed 24-weeks of their dietary intervention (see Figure 1). As such, quantitative and qualitative data will be collected concurrently during the intervention and follow-up period of the SWIFt study. A mixed-methods approach has been chosen to obtain different but complementary data on the research aims and to bring together the strengths of both methods (20–22).

**Figure 1 fig1:**
[figure not shown]
Mixed-methods evaluation design of the Shifting Weight using Intermittent Fasting in night shift workers study. RCT, randomized controlled trial; CER, continuous energy restriction; 5:2N, intermittent fasting protocol whereby the two fast days coincide with night shifts; 5:2D, intermittent fasting protocol whereby the two fast days coincide with day shifts and/or days off.

### Participants

3.1.

Eligibility criteria and recruitment for the overall SWIFt study has been previously described (11). In summary, study participants will be aged between 25 and 65 years and working a minimum of two nights per week for a minimum of six consecutive months. Participants will have a body mass index (BMI) of ≥28 kg/m^2^ for non-Asian men and women and ≥ 26 kg/m^2^ for Asian men and women and be able to attend either study site. Please refer to the previously published study protocol for exclusion criteria relating to medical and lifestyle conditions that may affect body composition, metabolism, or ability to follow the dietary protocol (11). Participants who consent to be invited to complete longitudinal audio diaries (LADs) and/or semi-structured interviews will be contacted after randomization based on a maximum-variation sampling approach (23). Maximum variation is used to provide a diverse set of participant viewpoints across age, sex, occupation, shift-type, and intervention group. Participants who discontinue with the intervention will also be invited for an interview. Identifying sample size *a priori* for qualitative research is problematic (24), therefore data collection and preliminary data analysis will occur concurrently, and recruitment will cease once maximum-variation is met, and when limited new information is identified.

### Data sources

3.2.

Key objectives and data sources used to meet the overall aim of this mixed-methods evaluation have been developed in line with similar evaluations (25) and are outlined in Table 1. Qualitative data will be collected and reported in line with the consolidated criteria for reporting qualitative research (COREQ) (26). It is anticipated that data collection will be complete by September 2023. For the purposes of this evaluation, participant “engagement” with the intervention is defined as whether participants: follow the general requirements of the study protocol (e.g., attendance of dietetic consults, self-monitoring); follow the dietary requirements of the intervention; and choose to continue with the intervention (e.g., rates of drop-out).

**Table 1 tab1:** Objectives, data sources and analysis for the evaluation of Shifting Weight using Intermittent Fasting in night shift workers (SWIFt) study.

Objective	Quantitative data source/analysis	Qualitative data source/analysis
1. To describe participant engagement overall and for each of the SWIFt weight loss interventions		
1.1 Dietary review attendance.	Number of dietetic reviews attended (Yes/No). Also described as percentage of reviews attended overall and by intervention group.	
1.2 Dietary goals.	Number of reviews where participant is following dietary goals as assessed by dietitian (Yes/No). Also described as percentage of reviews where goals are met overall and by intervention group.	
1.3 Dietary energy restriction.	Pre- and post-intervention energy restriction: 7-day food diary (baseline compared to 24-weeks and 18-months). Overall and by intervention group.	
1.4 Self-monitoring.	Number of checklists collected. Also described as percentage of food checklists collected overall and by intervention group.	
1.5 Other.	Frequency and percentage of participants who drop-out/time to drop out overall and by intervention group.	
2. Explore factors (intervention features, individual, social, organisational and wider environmental) that influence participant engagement for each of the SWIFt weight loss interventions.		
2.1 Intervention features.	Relationship between intervention group and engagement measures (1.1, 1.2, 1.3, 1.4, 1.5).	Semi-structured interviews. Longitudinal audio diaries (LADs). Features of intervention mapped to the BCT and TDF.
2.2 Contextual features.	Relationship between participant characteristics* and engagement measures (1.1, 1.2, 1.3, 1.4, 1.5). Participant reasons for drop-out.	Semi-structured interviews. Longitudinal audio diaries (LADs). Enablers/barriers to engagement mapped to the SEM.
3. Explore for who weight change outcomes are achieved for each of the SWIFt weight loss interventions and the influence of participant engagement.		
3.1 Intervention features.	Relationship between weight outcome and engagement measures (1.1, 1.2, 1.3, 1.4).	Participant interviews. Longitudinal audio diaries (LADs). Features of intervention mapped to the BCT and TDF.
3.2 Contextual features.	Relationship between participant characteristics* and weight outcome (24-weeks and 18-months).	Participant interviews. Longitudinal audio diaries (LADs). Enablers/barriers to outcomes mapped to the SEM.

^*^Participant characteristics include: age, sex, ethnicity, occupation, shift schedule, number of night shifts per fortnight; years in night shift; BCT, Behaviour Change Taxonomy; TDF, Theoretical Domains Framework; SEM, Social-Ecological Model.

#### Quantitative data sources

3.2.1.

The SWIFt study data will be entered primarily via direct data entry using Research Electronic Data Capture (REDCap; Vanderbilt University, Nashville, United States). REDCap is a secure web interface with data checks during data entry and uploading to ensure data quality and is housed on secure servers operated by Monash University, Australia.

##### Dietary review attendance

3.2.1.1.

Details of participant attendance at each dietetic consult/review will be recorded, including the following information: attendance or missed appointment, reasons for missed appointment (if known), and a summary of the discussion at the consult. Each participant will have a score out of 8 (the total number of dietetic reviews over the 24-weeks), representing the number of reviews attended. See Objective 1.1 in Table 1.

##### Dietary goals

3.2.1.2.

At each study visit, the study dietitian will judge and record (yes/no) whether the participant has followed the goals of their allocated dietary approach (e.g., followed the dietary changes recommended by the dietitian for the CER intervention, or consumed the study foods for each fasting period for the 5:2 diets). Each participant will have a score out of 8 (the total number of dietetic reviews over the 24-weeks), representing the number of reviews to have followed their dietary goals. See Objective 1.2 in Table 1.

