##### Researcher reflexivity

3.2.2.3.

Researcher reflexivity is an important component to allow for an awareness of how a researcher’s positionality may influence the research process, and to provide transparent and high-quality qualitative research (35, 36). The main researcher (CD) is an accredited practising dietitian undertaking this work as part of her PhD studies and has experience in both quantitative and qualitative research methods. CD will be involved in the wider SWIFt study as a researcher collecting data and as a study dietitian undertaking dietary consults with SWIFt participants. Reflexive diaries will be completed by the main researcher at key data points along the research process, including: after each participant interview, after reviewing participant LADs, and at each step of the data analysis process. Insights into this process will be discussed, as appropriate, at fortnightly meetings with the wider researcher team. This will allow documentation of key steps to the data collection and analysis process that can be reported as part of study results, adding transparency to the research process.

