### Data analysis

3.3.

Quantitative data on participant engagement (see Objective 1 at Table 1) will be analyzed for frequency/count and proportions or as overall daily energy restriction as described above. Regression models will be used to examine associations between engagement measures, participant characteristics (sex, age, ethnicity, occupation, shift schedule, number of night shifts per fortnight, years in night shift), intervention group, and weight change. It is anticipated that general linear regression models will be used for dependent variables that are continuous data and generalized linear regression models will be used for dependent variables that are count data. Differences in drop-out/time to drop out between intervention groups will be examined via survival curve analysis.

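### The yes/no diet-goal score comes from the coaching dietitian and is not required to be independent of weight progress, so its association with weight should be reported as rater-dependent

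*Protocol article*

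**What the plan says.** Section 3.2.1.2 (Dietary goals) of the protocol article states that at each study visit "the study dietitian will judge and record (yes/no) whether the participant has followed the goals of their allocated dietary approach". Two examples follow. For CER, the participant made the changes the dietitian advised. For the 5:2 diets, the participant ate the supplied foods on each fast. The yes answers are summed to a score out of 8. Table 1 row 1.2 describes the measure as "Number of reviews where participant is following dietary goals as assessed by dietitian (Yes/No").

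Section 2 (Intervention of interest) gives the dietitian's other tasks: "The dietitian will explain the dietary intervention, set goals with participants, discuss strategies to assist with dietary adherence, and monitor progress". Section 3.2.2.3 (Researcher reflexivity) adds that the main researcher of this evaluation collects trial data and is also one of the study dietitians.

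The score is used in Table 1 row 3.1: "Relationship between weight outcome and engagement measures (1.1, 1.2, 1.3, 1.4"). Section 3.3 (Data analysis) names the method: "Regression models will be used to examine associations between engagement measures, participant characteristics", intervention group and weight change. The objective above row 3.1 refers to the influence of participant engagement on weight outcomes.

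**The concern.** An exposure should be measured without knowledge of the outcome it is meant to explain. Here the rater has delivered the intervention, set the target being rated and followed the participant's progress. How much goal-following over two to four weeks counts as a yes is left to that rater. If progress in weight is known at the time, the same reported eating may be marked yes in someone who is losing weight and no in someone who is not. Part of the outcome would then sit inside the explanatory variable.

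The direction of such an error is predictable: toward an association between following goals and weight loss. The evaluation could take that pattern as support for the diets' active ingredient. The conclusion at stake is the 1.2 component of Objective 3.1. Attendance (1.1), diary-based energy intake (1.3) and checklist collection (1.4) do not rest on this judgement.

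**Working it through.** **1. The plan's own figure.** Section 2 schedules reviews "fortnightly for the first 8 weeks and then monthly for the last 16 weeks of the intervention period". Fortnightly over 8 weeks gives weeks 2, 4, 6 and 8 (4 reviews). Four-weekly over 16 weeks gives weeks 12, 16, 20 and 24 (4 reviews). 4 + 4 = 8, so the score maximum reproduces.

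**2. The chain of reasoning, link by link.**

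| Link | Where | Status |
|---|---|---|
| Dietitian sets goals, coaches, monitors progress | Section 2 | Stated |
| Dietitian makes the yes/no judgement | 3.2.1.2; Table 1 row 1.2 | Stated |
| Criteria are examples, with no threshold for the interval | 3.2.1.2 | Stated; concrete for 5:2, loose for CER |
| Score is related to weight outcome | Table 1 row 3.1; 3.3 | Stated |
| Masking, second rater or fixed order of judgement and progress | 3.2.1.2, 3.2.2.3, 3.3 | None described in the article |
| Dietitian knows weight change when judging | Section 2 (monitoring of progress) | Inferred, not stated |

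Two features come close to a safeguard. Reflexive diaries (3.2.2.3) are tied to interviews, audio diaries and analysis steps, not to this rating. Food checklists (3.2.1.4) record what was eaten and when, but only their collection is scored, and 3.2.1.2 does not name them as the basis of the judgement.

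**3. How large the distortion could be.** The article gives no rate of yes answers and nothing on rater behaviour, so every input here is an assumption. Both models simulate 200,000 participants with 8 judgements each.

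*Model A.* Weight progress in each interval is a standard normal variable with within-person correlation ICC. The person-level adherence shift has SD 0.15 and is unrelated to weight. The chance of a yes is 0.70 + adherence shift ± h/2, with plus after a better-than-average interval and minus otherwise. The result is the correlation r of the 0-8 score with total progress; the true value is 0.

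| h | r, ICC 0 | r, ICC 0.3 |
|---|---|---|
| 0.10 | 0.064 | 0.112 |
| 0.20 | 0.129 | 0.222 |

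Share of variance at the two ends: 0.064² ≈ 0.4% and 0.222² ≈ 4.9%.

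*Model B.* logit P(yes) = log(0.7/0.3) + A + log(OR) × W, where A is true adherence in SD units and W is weight loss to date in SD units. The result is the correlation of the score with final weight loss.

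| OR per SD of weight loss | True adherence-weight correlation 0 | True correlation 0.3 |
|---|---|---|
| 1 (no influence) | 0.00 | 0.23 |
| 1.25 | 0.11 | 0.33 |
| 1.5 | 0.20 | 0.40 |
| 2 | 0.32 | 0.49 |
| 3 | 0.46 | 0.59 |

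The tables show what a given degree of influence would do. They do not show that any influence exists.

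**The case against.** The strongest reply is that the decisive link is not in the document. No passage says weight is taken, viewed or discussed at dietetic consults. Section 3.2.1.6 lists weight for this evaluation at baseline, 24 weeks and 18 months only. Monitoring progress, placed after goals and adherence strategies, can equally mean progress with the diet. Visit procedures belong to the full trial protocol, which the article cites and which is not shown here. This stands. A reader might infer that the dietitian sees weight at every review and that the score is therefore contaminated; the document does not support that. It supports only a risk that the article's wording leaves open. One researcher's double role does not settle the matter either.

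Second, the criteria are not empty. For two of the three arms the example is a concrete behaviour. This also stands, and it makes the weakness greater for CER than for 5:2.

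Third, the analysis is exploratory, speaks of associations, uses four engagement measures and integrates sources to confirm or refute each other (section 3.3). That limits the damage to one measure. It does not repair that measure, because the integration step is not directed at this rating.

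Fourth, it may be too late. Section 3.2 expects data collection to be complete by September 2023. With a 12-month follow-up after the 24-week intervention, the last rated consult would fall around September 2022. Re-ordering consults may therefore be moot, whereas reporting can still change.

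That an analysis plan might cover this is a weaker reply: who rates measure 1.2, and how, is defined in this article.

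**Conclusion.** The point holds as a risk to one measure. The coaching dietitian makes a judgement with example-only anchors, the article does not require it to be independent of weight progress, and the score is then related to weight. If weight change is known to the rater, the 1.2-weight association is biased toward a link between following goals and losing weight. The size is unknown: about 0.06 to 0.22 in correlation under Model A, and up to 0.46 under the strongest assumption in Model B, where the truth is zero. These ranges are illustrative and rest wholly on assumed rater behaviour.

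A reader might go further and hold that Objective 3.1 as a whole is undermined. It is not, since 1.1, 1.3 and 1.4 do not depend on this judgement. What cannot be supported is reading the 1.2 association alone as the influence of engagement on weight.

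**What to change.** **Consults still to come, if any.** State in 3.2.1.2 that the yes/no is entered in REDCap from the participant's report and the food checklist before that visit's weight or progress is viewed or discussed. Add one field for whether weight was already known. Record the date of the change, because a change part-way puts two rating procedures into one 0-8 score.

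**All data, including completed visits.** In Objective 3.1, present the 1.2-weight association as rater-dependent. Show the objective also without 1.2, using 1.1, 1.3 and 1.4. State that 1.2 alone is not evidence that engagement influenced weight.

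**Cost.** A change in consult order, one REDCap field, one additional analysis and a limitation statement, with no extra visits or staff. The change in order is only a partial remedy, because the dietitian's memory of earlier progress remains. The reporting change is therefore needed in any case.

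### Goal-following is a study dietitian's yes/no judgement, but the listed regression variables include neither dietitian nor site; if caseloads differ, rater strictness can be reported as a participant effect

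*Protocol article*

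**What the plan says.** Section 3.2.1.2 (Dietary goals) of the protocol article defines measure 1.2. At each visit "the study dietitian will judge and record (yes/no) whether the participant has followed the goals of their allocated dietary approach". The criteria are given as examples and differ by arm: "followed the dietary changes recommended by the dietitian for the CER intervention, or consumed the study foods for each fasting period for the 5:2 diets". The yes answers are added up to a score out of 8. The article describes no calibration of raters and no second rating.

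Table 1 uses this score as an outcome twice: against intervention group (row 2.1) and against the participant characteristics (row 2.2). Section 3.3 (Data analysis) lists the variables that the regression models will relate to one another. Besides the measures of engagement, these are: "participant characteristics (sex, age, ethnicity, occupation, shift schedule, number of night shifts per fortnight, years in night shift), intervention group, and weight change". Neither dietitian nor site is on that list.

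The article does not give the number of dietitians, but it points to more than one. Participants must "be able to attend either study site" (section 3.1), and the main researcher will act "as a study dietitian undertaking dietary consults with SWIFt participants" among other roles (section 3.2.2.3). Section 5 lists approvals from a Melbourne health service, the University of South Australia and the research committee of a Victorian ambulance employer.

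**The concern.** Where the outcome is a person's opinion, the person giving it is a source of variation. If one dietitian says yes more readily than another, and each participant is seen mainly by one dietitian, all eight of that participant's ratings shift together.

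That shift only adds noise if every dietitian sees the same mix of participants. It becomes bias if the mix differs. Suppose that one site recruits mostly from one occupation and that its dietitian is the stricter one. The occupation would then seem to follow its goals less well, although its behaviour is no different. Row 2.2 is meant to show who engages with the diets, so such an artefact would go straight into the conclusions about whom the interventions suit.

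The randomised comparison in row 2.1 is less exposed. If dietitians see all arms, randomisation balances the raters across diets in expectation.

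**Working it through.** **The plan's own figure.** Section 2 has participants "see a study dietitian fortnightly for the first 8 weeks and then monthly for the last 16 weeks of the intervention period". With monthly taken as every four weeks, that is 8/2 + 16/4 = 4 + 4 = 8 reviews, which matches the stated maximum score.

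**Inputs the article does not give.** Sample size, number of dietitians, their allocation to participants and their agreement are all assumed below. The results are therefore a range, not an estimate for this trial.

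**Size of the bias.** Take two dietitians. Let g be the gap in their probability of recording yes, and let s1 and s0 be the shares of two participant groups seen by the stricter one. With no true group difference, the expected spurious difference on the 0 to 8 scale is, in absolute size,

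8 × g × (s1 − s0).

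| g | s1 − s0 = 0 | 0.2 | 0.4 | 0.8 |
|---|---|---|---|---|
| 0.05 | 0.00 | 0.08 | 0.16 | 0.32 |
| 0.10 | 0.00 | 0.16 | 0.32 | 0.64 |
| 0.20 | 0.00 | 0.32 | 0.64 | 1.28 |

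For example, 8 × 0.10 × (0.7 − 0.3) = 0.32 points.

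**False-positive rate, two dietitians.** Simulation with 1,000 runs per cell, no true effect, participants' probabilities drawn from Beta(6,4), and a linear model with robust standard errors at two-sided 0.05. The Monte Carlo standard error at 5% is √(0.05 × 0.95/1,000), about 0.7 percentage points.

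| N | g | Shares seen by stricter dietitian | No dietitian term | With dietitian term |
|---|---|---|---|---|
| 100 | 0.10 | 50% vs 50% | 6.3% | 5.0% |
| 100 | 0.10 | 70% vs 30% | 15.9% | 5.3% |
| 100 | 0.10 | 90% vs 10% | 43.4% | 10.0% |
| 100 | 0.20 | 50% vs 50% | 6.4% | 4.9% |
| 100 | 0.20 | 70% vs 30% | 37.9% | 6.1% |
| 100 | 0.20 | 90% vs 10% | 93.8% | 8.7% |
| 200 | 0.10 | 50% vs 50% | 5.6% | 4.6% |
| 200 | 0.10 | 70% vs 30% | 26.4% | 5.3% |
| 200 | 0.10 | 90% vs 10% | 70.8% | 7.0% |
| 200 | 0.20 | 50% vs 50% | 5.1% | 5.3% |
| 200 | 0.20 | 70% vs 30% | 63.2% | 5.8% |
| 200 | 0.20 | 90% vs 10% | 99.9% | 7.6% |

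At a fixed imbalance the unadjusted rate rises with N, as expected of a bias: a larger sample does not help. With the term, the mean estimated effect lies between −0.02 and +0.02 points in every cell. The rates of 7% to 10% in the 90% vs 10% rows arise where few participants separate the two factors. At N = 100 about 100/2 × 0.1 = 5 people fall in each off-diagonal cell, too few for robust standard errors to be reliable.

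**A different set of assumptions.** N = 200, eight ratings each, dietitian effects drawn at random on the logit scale, participant SD 1, and 1,500 runs per setting.

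- Four dietitians, prevalence of the characteristic from 20% to 80% across caseloads: 12.3%, 17.3% and 32.6% for rater SD 0.3, 0.5 and 0.8.
- Four dietitians, prevalence from 40% to 60%: 5.3%, 6.0% and 9.0%.
- Two dietitians, rater SD 0.5: 43.3%.
- With a dietitian term: 4.5% to 6.3%.

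Both sets agree. There is little or no inflation when caseloads are similar, marked inflation when they are not, and a dietitian term removes most or all of it.

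**The case against.** **The article is a summary.** Section 3.3 names variables of interest and gives no model formula, and adjustment terms are often left to an analysis plan. This stands in part: the list cannot be read as a closed specification. But the sentence naming the variables is definite. The wording that marks the models as anticipated belongs to the next sentence, on which type of regression to use. Section 3.2.1.1 also itemises the consult record without naming the rater, although that list need not be complete.

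**Caseloads are unknown.** A reader might infer that strictness will show up as an effect of occupation. The article does not support that. It would need several raters, participants tied largely to one of them, raters who differ, and caseloads that differ on the characteristic. Several raters are a fair inference, and the ambulance employer's approval makes a link from occupation to site to rater plausible. None of the four conditions is demonstrated.

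**Other engagement measures.** A reader might extend the point to attendance (1.1) and checklist collection (1.4). These are recorded events, not judgements. If a dietitian's skill changes attendance, that is a real influence on engagement and not rater error.

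**The rating has anchors.** The examples in section 3.2.1.2 and the food checklist collected at the same visits limit how far raters can diverge, and diary energy intake (1.3) is a separate measure. This bears on how large the gap between raters is. It does not rule one out.

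**The aims are exploratory.** This is true, and findings are to be set beside the qualitative data. It limits the consequence but does not make a biased coefficient informative.

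**Conclusion.** The point holds in conditional form and for measure 1.2 only. A subjective rating, probably made by several dietitians, is to be related to participant characteristics, and no dietitian or site variable is listed. Where caseloads are alike, the harm is little or none: a false-positive rate of about 5% to 6%. Where they are strongly unbalanced, the assumed scenarios give roughly 12% to 63%, with spurious differences of 0.32 to 0.64 points out of 8 at a 70% vs 30% split and a strictness gap of 0.10 to 0.20. The 90% vs 10% scenarios go higher still, but there dietitian and characteristic are almost the same variable. Every one of these figures rests on assumed inputs, and the article does not show where this trial lies in the range.

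It would also be too strong to claim that a dietitian term can only improve precision. If raters do not differ, it costs a little. Nor does the term cure a separate problem in section 3.2.1.2: what counts as yes differs between CER and 5:2, whoever rates. This is a cheap and worthwhile improvement, not a fault that invalidates the evaluation.

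**What to change.** 1. Record the rating dietitian's study ID with each consult, or recover it from consult records for visits already held.
2. In the models for measure 1.2 in rows 2.1 and 2.2, include dietitian as a fixed term, or as a random term if there are many. If each site has a single dietitian, use site. The two effects then cannot be told apart, but one term removes both from the participant coefficients.
3. Tabulate the characteristics by dietitian and site. Where one is nearly collinear with either, report that the two cannot be separated, and do not present a participant effect.
4. Leave the models for 1.1 and 1.4 as they are, or add the term there as a sensitivity analysis only.

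The cost is one data field, one model term with K-1 degrees of freedom for K dietitians, and possibly a small loss of precision if raters do not differ. A site term would also absorb any real difference between sites.
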